## Abstract

**Background:**

A series of studies suggests that immersive virtual reality (IVR) can enhance perspective-taking and behavioral change by simulating real-world scenarios experienced from different points of view. IVR has emerged as a promising tool for the prevention of gender-based violence, including sexual harassment. However, evidence on the effectiveness of first-person embodiment–based interventions in fostering empathy and modifying gender-related attitudes remains limited.

**Objective:**

This study aims to evaluate the efficacy of REVISE (Realidad Virtual Inmersiva y Sexualidad), an IVR-based intervention designed to influence beliefs related to sexual aggression and related psychosocial mechanisms in heterosexual men through partner identity exchange.

**Methods:**

Ninety heterosexual couples will be randomly assigned to one of three experimental conditions: (1) IVR with partner identity exchange in a sexual harassment scenario, (2) IVR with partner identity exchange in a neutral scenario, or (3) third-person observation of a sexual harassment scenario. The intervention consists of a single IVR session, with assessments conducted at baseline, postintervention, and at 3-month follow-up. Data will include self-report questionnaires, physiological measures (eye tracking and pupillometry), and semistructured qualitative interviews. The primary outcome is the change in beliefs related to sexual aggression. Secondary outcomes include empathy, gender role attitudes, relationship functioning, and physiological responses.

**Results:**

At the time of manuscript submission, recruitment had not yet begun. The study is expected to generate quantitative and qualitative data on changes in beliefs related to sexual aggression, empathy, gender-related attitudes, and physiological responses across experimental conditions.

**Conclusions:**

The REVISE trial will contribute to the evidence base on IVR interventions for the prevention of gender-based violence. By integrating embodiment, behavioral simulation, and multimodal assessment, this study may inform the development of future technology-based interventions aimed at promoting gender-equitable and prosocial behaviors.

**Trial Registration:**

ClinicalTrials.gov NCT06839937; https://clinicaltrials.gov/study/NCT06839937

**International Registered Report Identifier (IRRID):**

PRR1-10.2196/91993

## Introduction

Violence against women (VAW) is defined as any behavior that results in or is likely to result in physical, sexual, or psychological harm to a woman [1,2]. It is estimated that approximately 1 in 3 (30%) women worldwide have experienced some form of physical or sexual violence by an intimate partner—or even by a stranger—at some point in their lifetime [2]. Some of the short- or long-term consequences for survivors include posttraumatic stress, depression, anxiety, interpersonal difficulties, suicide, gynecological problems, induced abortions, unintended pregnancies, pain-related syndromes (eg, back, pelvic, or abdominal), gastrointestinal disorders, reduced mobility, increased substance abuse, smoking, and risky sexual behaviors that may facilitate sexually transmitted infections [1-5]. Additionally, VAW has broader social consequences, such as unemployment, poverty, homelessness, stigmatization, physical aggression, and femicide [1,5,6]. Some behaviors perpetrated by aggressors include humiliation, isolation, threats, and actions that restrict a woman’s autonomy [5], which often intensify over time.

Gender-based inequities have long facilitated gaps between traditional gender roles (ie, masculinity and femininity), historically privileging masculinity and, consequently, those to whom this gender has traditionally been assigned—men [7]. This disparity can lead to a lack of awareness or even a denial of inequitable gender gaps. A recent study conducted in Spain showed that men tend to minimize the impact of gender-based inequalities [8]. In fact, 3 out of 10 men believe that a partner can limit freedom and normalize jealousy as a sign of love. In addition, a considerable proportion of men (18.1%) validate controlling behaviors, such as checking their intimate partner’s cell phone [8]. Another study conducted in Mexico found that 44% of men did not perceive gender inequities [9]. These findings align with those reported by Rodríguez et al [8], where only 50.4% recognized VAW as a serious social problem in 2021. These data underscore the persistence of the sexist and traditional perspectives that shape men’s interaction with women and reinforce the rigid roles that contribute to VAW.

These numbers highlight the urgent need to intervene in traditional male perspectives to address VAW. Although some male-focused education programs designed to prevent gender-based violence focused on males have led to a decrease in physical and sexual violence, attitudes related to gender roles (eg, protection, partner control, and male provider) have proven to be particularly resistant to change [10]. This challenge is further highlighted in Ruane-McAteer et al [11,12] review, which focused on gender-transformative approaches, as it highlights the lack of high-quality interventions and the existence of inconclusive findings in relation to the efficacy of this type of intervention. Such evidence reinforces the need for robust experimental designs supported by qualitative evaluations, moving beyond psychoeducational strategies that focus solely on knowledge acquisition or attitude change [13,14]. Instead, interventions must effectively target behavioral change, ensuring that such changes can be rigorously assessed.

Virtual reality (VR) presents a promising tool for interventions targeting psychological mechanisms associated with VAW, as it facilitates ecologically valid experimental settings that allow individuals to experience realistic situations without actual exposure (ie, overcoming ethical barriers) [15,16]. Moreover, VR is recognized as a tool that can foster attitudinal, cognitive, and behavioral changes [17-19]. This methodology has been used previously and has shown effects on emotion recognition, a process potentially underlying aggressive behavior [20]. VR has also been used to replicate Milgram’s obedience experiments [21], analyze bystander response to violence [22], study intimate partner violence [23-25], and assess sexual behaviors in pedophiles [26].

Although several studies have shown the benefits of VR across different perspectives, few have explored its potential for harassment prevention through perspective-taking experiences. Of the earlier studies, one focused on increasing the realism of role-playing exercises designed to teach women how to respond effectively to harassment [27], while another aimed to develop skills for responding to sexual harassment in a simulated job interview [28]. Other studies have focused on assessing whether exposure to violence in VR has a greater impact than traditional media, but their results have been inconclusive, potentially due to limitations in evaluation methods and design [29]. However, some research suggests that VR is more effective than other approaches (eg, narrated experiences) in enhancing empathy and perspective-taking among men [30]. These findings highlight the VR’s potential as a transformative therapeutic tool for VAW prevention.

Current research has focused on whether VR exposure itself fosters changes in prosocial behaviors or whether the key factor is perceiving simulated scenarios from a first-person perspective (ie, immersive virtual reality [IVR]). Some studies have shown that virtually embodying the role of a person experiencing sexual harassment can positively influence the reduction of aggressive behaviors [30]. Therefore, the results seem to indicate that IVR could actively engage men in preventing aggressive behaviors by providing them with firsthand experiences of harassment [31], making it a valuable tool for fostering empathy and perspective-taking as a mechanism for behavioral change.

The present project examines the effectiveness of an IVR-based intervention, REVISE (Realidad Virtual Inmersiva y Sexualidad), designed to influence psychological mechanisms associated with sexual harassment and VAW. Specifically, the intervention seeks to reduce beliefs that legitimize or minimize sexual aggression while promoting empathy and perspective-taking through immersive partner identity exchange scenarios. In this intervention, male participants embody the virtual perspective of their partner in simulated harassment situations, allowing them to experience the interaction from the survivor’s viewpoint. This intervention will be designed primarily because of the critical need for a tool that

Incorporates a dyadic perspective: The presence of both partners in the intervention is expected to amplify the emotional impact and enhance perspective-taking due to their pre-existing emotional bond. Moreover, this is the first study to use partner embodiment rather than an anonymous avatar.Target intimate partner violence: Since VAW often occurs within romantic relationships, involving both partners provides a direct and contextually relevant approach to addressing intimate partner violence.Aligns with gender synchronization principles: International recommendations suggest the inclusion of men in VAW prevention.Is grounded in psychological theory: REVISE includes a module that seeks to model positive partner-guided relational behaviors. This component allows behavioral changes to be fostered through a virtual experience.

## Methods

### Objectives

The primary objective of this randomized controlled trial is to evaluate the efficacy of the REVISE intervention in reducing beliefs that legitimize or minimize sexual aggression (Acceptance of Modern Myths About Sexual Aggression [AMMSA] scale) among heterosexual men at postintervention and at 3-month follow-up.

The secondary objectives are

To evaluate the effects of the REVISE intervention on empathy, gender role attitudes, relationship functioning, and communication patterns.To assess changes in physiological responses (eye tracking and pupillometry) during the IVR experience across experimental conditions.To explore participants’ subjective experiences and perceived changes following the intervention through qualitative interviews, and to integrate these findings with quantitative outcomes.

It is hypothesized that participants exposed to identity-swapping with sexual harassment scenarios will show greater reductions in beliefs legitimizing sexual aggression compared to the control conditions.

### Study Setting

This study will be conducted at the Interdisciplinary Research and Innovation Hub of the Universitat Oberta de Catalunya. This hub is 2700 square meters and is equipped with research and support staff, as well as 8 laboratories. The XR-Lab is one of the laboratories that provides the infrastructure needed to carry out the intervention sessions. It includes a monitoring system that allows the evaluation of 3 people simultaneously. Participants will be evaluated within this hub.

### Sample

Ninety heterosexual couples will participate in the study. All persons must be between the ages of 18 and 39 years, be in a relationship for at least 6 months, and give explicit consent to participate in the research, for which they must be able to read and write in Spanish. Individuals who have any physical condition that may hinder the use of the equipment (ie, epilepsy); who are currently experiencing severe psychological distress related to past harassment experiences, high levels of relationship distress, or problematic substance abuse; or who have significant mental health difficulties requiring intensive treatment will not be able to participate in the study. Participation will be encouraged through open calls on social media, where interested individuals will fill out an online form to determine their eligibility based on the inclusion and exclusion criteria. Those who meet the criteria will be invited to participate in the study. Couples who decide to participate will receive an economic compensation of €50 (US $54) at the end of the trial. No specific concomitant interventions are prohibited during participation, although participants are advised to avoid other IVR exposures during the trial period to prevent cross-contamination of experience.

This study is designed as a randomized, parallel-group, superiority trial with 3 arms and a 1:1:1 allocation ratio. An a priori power analysis was conducted to determine the necessary sample size to detect a meaningful effect in the primary outcome measure. Considering the study design, an estimated effect size of *d*=0.4, statistical power of 0.9, and α level of .05, the required sample size was calculated to be 84 heterosexual couples. To account for potential attrition (estimated at 7%), a total of 90 couples will be recruited. While the a priori power calculation was based on a standard framework, the final sample (N=180 individuals; 90 units of randomization and 30 couples per experimental condition) was increased to provide additional robustness for the planned longitudinal and dyadic analyses. The sample size estimation was based on a conservative effect size derived from prior studies. Although the calculation does not explicitly model the multilevel structure of the data (ie, repeated measures nested within individuals and couples), the use of mixed-effects models in the analysis phase is expected to appropriately account for this dependency structure. The allocation sequence will be computer-generated using random block sizes of 3 or 6 by a research assistant not involved in recruitment, assessment, or intervention delivery. Allocation will be concealed until participant enrollment and completion of baseline assessments (see Figure 1).

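### The stated inputs (d = 0.4, 90% power, 5% alpha, three equal arms) do not give 84 couples: unadjusted power for d = 0.4 between two arms of 28 men is about 31%

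*Protocol article*

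**What the plan says.** Protocol article, Methods, Sample: the design is a "superiority trial with 3 arms and a 1:1:1 allocation ratio". The calculation is given as "estimated effect size of *d*=0.4, statistical power of 0.9, and α level of .05, the required sample size was calculated to be 84" couples. Ninety couples are to be recruited to allow for 7% attrition, which is 30 per arm. The section adds that "The sample size estimation was based on a conservative effect size derived from prior studies", and that the final sample "was increased to provide additional robustness for the planned longitudinal and dyadic analyses". It concedes that repeated measures and couples were not explicitly modelled. It names no test, no sidedness, no contrast and no correlation.

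Under Objectives, the primary outcome is the AMMSA score in heterosexual men after the intervention and at 3 months, and the hypothesis is a larger reduction in condition 1 than in the control conditions. Under Primary Analysis, the comparison is condition by time over three conditions and three time points.

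**The concern.** Eighty-four couples in three equal arms is 28 men per arm. That is far too few to detect a standardised difference of 0.4 between two arms with 90% power by any ordinary unadjusted test. Either the printed effect size is not the one that produced 84, or the calculation rests on assumptions the article does not give.

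The stated power tells readers how to interpret a null result. If the trial has 90% power for d = 0.4, a null result counts against an effect of that size. If power is nearer one third, it says little. The reassurances around the figure (a conservative effect size, extra robustness, 180 individuals) point the same way and do not repair it.

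**Working it through.** **Inputs.** d = 0.4, power 0.90, alpha 0.05, three arms at 1:1:1, 84 couples required, 7% attrition and 90 recruited, all from Sample. The population is one man per couple, from Objectives. Two-sided testing is my assumption. Power uses the exact noncentral t or F distribution.

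**1. What reproduces 84.**
- One-way ANOVA, three groups, f = 0.4, noncentrality f²N = 0.16N. Power is 0.895 at N = 81 and 0.907 at N = 84, so 84 is the first balanced N at or above 90%.
- Repeated-measures interaction, f = 0.2, two time points, correlation 0.5. The noncentrality is f²·N·m/(1−ρ) = 0.04 × N × 2/0.5 = 0.16N, the same test, so again 84. With the planned three time points this variant gives 69.

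In both, the effective f is 0.4. For three groups this converts to a largest pairwise difference of:
- one arm differs from the other two: 0.4 × 3/√2 = 0.85 SD
- evenly spaced arms: 0.4 × √6 = 0.98 SD

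In the second calculation these are differences in change; at ρ = 0.5 the SD of change equals the SD of a single measurement.

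**2. What d = 0.4 gives without baseline adjustment.**
- Two arms of 28: noncentrality 0.4 × √(28/2) = 1.50, power 0.312. With 30 per arm, 0.332.
- Ninety per cent power needs 133 men per arm. The smallest d with 90% power at 28 per arm is about 0.88.
- Condition 1 (28) against pooled controls (56): noncentrality 0.4 × √(28 × 56/84) = 1.73, power 0.401.
- Three-arm omnibus: d = 0.4 corresponds to f = 0.4/√6 = 0.163 up to 0.4 × √2/3 = 0.189. Power at N = 84 is 0.241 to 0.310; 90% needs 480 to 360 men.

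**3. What baseline information could add.** Suppose d = 0.4 is in raw SD units and ρ is the baseline–follow-up correlation. The effective d is 0.4/√(2(1−ρ)) for a change score and 0.4/√(1−ρ²) for ANCOVA. The article gives no ρ, so a range is shown.

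| ρ | 28 v 28, change | 28 v 28, ANCOVA | 28 v 56, change | 28 v 56, ANCOVA |
|---|---|---|---|---|
| 0.5 | 31% | 40% | 40% | 51% |
| 0.7 | 48% | 54% | 60% | 67% |
| 0.8 | 64% | 69% | 77% | 81% |
| 0.85 | 77% | 80% | 88% | 90% |
| 0.87 | 82% | 85% | 92% | 93% |
| 0.9 | 91% | 92% | 97% | 98% |

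Ninety per cent is reached near ρ = 0.9 for a pairwise contrast and near 0.85–0.87 against pooled controls.

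**4. The six extra couples.** 90 × 0.93 = 83.7. After the planned attrition about 84 remain, which is the stated requirement with no surplus.

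**The case against.** The article names no test, so it is tempting to conclude that f = 0.4 was mislabelled as d = 0.4. The document does not establish that. The two-time-point calculation uses f = 0.2, which is the usual two-group conversion f = d/2 of the printed d, and needs no mislabelling. Against it, the Sample section says repeated measures were not explicitly modelled, and the trial has three time points. The source cannot be settled from the text. What stands is that both calculations imply the same detectable difference.

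It is also fair to say that 31% is not the power of the planned model. That model uses baseline and two later assessments, and the hypothesis may be read as condition 1 against both controls together. Power could then be much higher, and a high correlation is less implausible immediately after a single session than at 3 months. So the documents do not support a flat statement that the trial will miss d = 0.4. But the article states no correlation, and 90% needs one of about 0.85 or more.

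The effect size may itself be conservative: if 0.4 was the effect truly intended, the fault lies in the number of couples and the word could stand.

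Finally, the primary model's random intercepts for participants nested within couples suggest that both partners' scores are modelled. That sits awkwardly with an objective confined to men, but it is a separate matter and does not make 180 the sample size for an effect in men.

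**Conclusion.** The power statement is wrong as written. For a between-arm comparison in men, d = 0.4 with 28 per arm gives, without baseline adjustment, about 31% power pairwise (33% with 30 per arm), about 40% against pooled controls and 24–31% for the omnibus test, not 90%. The figure of 84 corresponds to a largest between-arm difference of about 0.85–0.98 SD, more than twice the printed effect.

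These figures assume two-sided 5% tests and one man per couple. They would be more favourable if a high baseline–follow-up correlation were declared and justified. This is not detail left to a fuller document: the article asserts an effect size, a power and a sample size that do not fit together. How the mismatch arose remains open.

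**What to change.** Keep 90 couples and correct the Sample section:

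- State the test, contrast, sidedness, effect metric (f or d; endpoint or change; raw or change-score SD) and any correlation actually used to obtain 84.
- Restate the effect detectable with 90% power, about 0.88 SD pairwise with 28 men per arm unadjusted, and give the power for d = 0.4 over a declared range of correlations for each primary contrast.
- Remove the claim of additional robustness; the six extra couples cover attrition only.
- Say that the primary objective rests on one man per couple: 90 randomised, about 84 after attrition.
- Keep the word conservative only if it describes the effect size the calculation really used.

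The cost is wording, with no extra couples and no change to the design or analysis. The stated power or detectable effect will look less favourable. The article reports that recruitment had not started as of January 2026, so the correction can be made before data exist.

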#### Change in Body Ownership Illusion

To assess body ownership and agency from a first-person perspective, a validated 4-item scale will be administered verbally at two time points during the IVR experience (see Figure 1 and Table 1):

Mirror embodiment phase: The assistant will ask participants to look at a virtual mirror and rate, on a scale from 0 to 10, the extent to which they felt that the virtual body reflected in the mirror was their own. Participants will then look down and respond to the same question regarding their virtual bodies.Farewell phase: At the end of the IVR session, participants will answer two additional questions: “Did you feel that you owned a different body during the experiment?” and “Did you feel fear of aggression at any point in the experiment?” on the same scale (0-10).

**Table 1 table1:** Trial schedule.

Time point	Preintervention	Allocation	Postallocation		
		0	Intervention day	1 week after intervention^a^	3 months follow-up^b^
Enrollment	✓				
Eligibility screen	✓				
Informed consent	✓				
Allocation randomization		✓			
Baseline			✓		
Embodyment task			✓		
IVR^c^ exposure condition 1			✓		
IVR exposure condition 2			✓		
IVR exposure condition 3			✓		
Self-report assessment^d^			✓	✓	✓
Physiological measures (eye-tracking and pupillometry)			✓		
Change interview			✓	✓	✓

^a^The 1-week postintervention evaluation examines short-term retention of intervention effects.

^b^The 3-month follow-up was chosen to assess long-term changes.

^c^IVR: immersive virtual reality.

^d^Self-report assessments include Interpersonal Reactivity Index (IRI), Ambivalent Sexism Inventory (ASI), Communication Patterns Questionnaire (CPQ), Acceptance of Modern Myths About Sexual Aggression (AMMSA) Scale, Dyadic Adjustment Scale (DAS), Couple Flourishing Measure (CFM), Self-Assessment Manikin (SAM), and body ownership.

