#### Condition 3: Third-Person Observer

Participants will observe a scene of sexual harassment in a virtual environment, but this time from a third-person perspective since they will embody their own avatar. The purpose will be to assess how observation of harassment affects participants’ attitudes toward sexual harassment and their empathetic responses to the survivor.

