### Intervention Procedure

The intervention follows 5 phases, as shown in Figure 1. Each participant will arrive at the laboratory and provide their consent to participate in the study. They will be randomly assigned; participants will be naïve to the study hypotheses. While avatar creation takes place, the couple will answer preintervention questionnaires. Phase 1 also involves the process of personification of the avatar according to the condition in which they will be assigned (see the section on the Intervention Description).

During phase 2, the participants will perform a mirror embodiment task to familiarize themselves with the virtual environment and their new virtual body. More specifically, a female virtual assistant will welcome the participants and instruct them to perform some physical body movements while observing themselves in a virtual mirror. The observation of real-time movements in the embodied avatar, which corresponds to the participants’ real body movements, will allow for greater immersion, as well as enhance body ownership and agency toward the virtual body. For assessment purposes, the female assistant will be a sexualized avatar. During this initial outreach, eye-tracking data will be collected from the participants in relation to the assistant’s cleavage, as gaze fixation on sexualized body parts has been identified as a marker of sexual objectification [47,52]. Once the training and embodiment process is completed, participants will be asked the first questions related to embodiment to check the degree of embodiment achieved.

In phase 3, men will have a 180-second adaptation period in which they will be in an empty bar, and nothing will happen, while women will be in a neutral playful setting in all 3 conditions. Condition 1 men will be involved in a situation of sexual harassment by a group of other men (eg, unwanted flirting, verbal intimidation, and sexist comments). In condition 2, they will stay the same length of time as in the other conditions, but in this case, they will not be sexually harassed. Finally, those in condition 3 will witness the same harassment as in condition 1, but from a bystander perspective, that is, the assaulted person will be a random virtual woman. While people are exposed to the scenarios, their emotional arousal will be assessed by pupillometry in the 3 experimental conditions; however, SAM will be used at the end of phase 3.

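### Allocation is promised to stay concealed until baseline is complete, but Table 1 and the session procedure place baseline after allocation and do not say when the arm is revealed

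*Protocol article*

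**What the plan says.** Three places in the Protocol article bear on the order of allocation and baseline.

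- **Sample:** "Allocation will be concealed until participant enrollment and completion of baseline assessments". The sequence is generated by a research assistant who has no part in recruitment, assessment or delivery.
- **Table 1 (trial schedule):** the row "Allocation randomization" is ticked in the allocation column, time 0. The Baseline row is ticked under "Intervention day", the first of the postallocation columns, together with the embodiment task and the IVR exposures.
- **Intervention Procedure:** after arrival and consent, "They will be randomly assigned; participants will be naïve to the study hypotheses". The next sentence reads: "While avatar creation takes place, the couple will answer preintervention questionnaires". The one after it reads: "Phase 1 also involves the process of personification of the avatar according to the condition in which they will be assigned".

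Avatar use depends on the arm. In conditions 1 and 2 the man embodies his partner's avatar. In condition 3 he observes "from a third-person perspective since they will embody their own avatar".

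Under Primary Analysis, the comparison of interest is the condition-by-time interaction, with baseline as the reference level of time.

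**The concern.** The Sample section and the two operational descriptions cannot all be followed as they are written. Staff working from Table 1 and the procedure would randomize first and collect the questionnaires afterwards, during a phase that also contains a step carried out by condition. Nothing in those two places tells them to withhold the arm until the questionnaires are finished.

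The baseline AMMSA score is at stake. It is a self-reported attitude measure on a sensitive subject, and every primary contrast is a change from it. If a man knew, or could work out from the avatar preparation, that he was about to take his partner's body, his baseline answers might shift. Such a shift would enter the change contrast at both the postintervention and the 3-month time points, and the analysis could not remove it afterwards.

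**Working it through.** The article gives no figure for this point, so the check is a comparison of passages followed by a short piece of algebra.

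**Step 1. Order of events by place**

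| Place | Order stated or implied |
|---|---|
| Sample | baseline complete, then allocation revealed |
| Table 1 | allocation (time 0), then baseline (postallocation, day of intervention) |
| Intervention Procedure | consent, assignment mentioned, then questionnaires during avatar creation; personification by condition in the same phase |

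Two places put baseline after allocation. One says that allocation stays hidden until baseline is done. These agree only if the allocation is drawn at time 0 and kept from everyone in the session until the questionnaires are complete. The article does not state that step.

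**Step 2. Who could know the arm during the questionnaires**

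- *Couples.* The procedure says that participants are naive to the hypotheses. It does not say whether they are naive to their arm, and no passage says that they are told it before answering.
- *Session staff.* The questionnaires are tied to avatar creation. Personification according to condition belongs to the same phase, but its order relative to the questionnaires is not given. If the two overlap, whoever carries out the personification must know at least exchange versus no exchange before baseline is complete. The separation of roles in the Sample section covers only the person who generates the sequence.

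**Step 3. How a leak would enter the primary contrast**

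Let *b*ₖ be the shift in mean baseline AMMSA in arm *k* caused by knowledge of the arm. It is zero if the arm stays hidden. With baseline as the reference level of time, the expected change contrast between arms *j* and *k* is

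observed contrast = true contrast − (*b*ⱼ − *b*ₖ).

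- Conditions 1 and 2 share the exchanged avatar. For a leak through the avatar alone, *b*₁ and *b*₂ should be about equal, and the 1-versus-2 contrast is largely untouched.
- Condition 3 uses the man's own avatar, so *b*₁ − *b*₃ need not be zero. The 1-versus-3 contrast, which Trial Design relies on to isolate embodiment from exposure, is the one exposed.
- A downward shift in condition 1 would shrink an apparent reduction in AMMSA. An upward shift, for example from reactance, would enlarge it. The article gives neither sign nor size for *b*₁ − *b*₃.

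**The case against.** The strongest reply is that drawing an allocation is not the same as disclosing it. The Sample section governs disclosure; Table 1 and the procedure give only the time of randomization. A sequence prepared by an uninvolved assistant, drawn at time 0 and withheld until baseline ends, is ordinary practice. The procedure also refers to assignment in the future tense, and Figure 1, which the Sample section cites at this point, is not available here.

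Second, avatar creation need not reveal anything. The couple meets virtually in every condition, so each couple may need one male and one female likeness whatever the arm, and the arm may decide only who wears which. Third, AMMSA is completed by the participant, so staff knowledge alone has no stated route into the score.

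Much of this stands, and it limits the point. A reader might infer that baseline AMMSA already carries the allocation. The text does not support that, because disclosure to couples before the questionnaires is nowhere stated. A reader might also infer that the female partner's relationship scores, used as covariates, are spoiled by being measured after randomization. A measurement taken after a draw that is still concealed is not affected by treatment, so timing alone does no harm. Nor is there support for a claim that the arms differ through dropout between allocation and baseline: the procedure describes these steps together on arrival at the laboratory, and differential exit would require knowledge of the arm.

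The reply does not supply the missing step. The reading that reconciles all three places has to be constructed by the reader, and the schedule table as printed still runs against the rule in the Sample section.

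**Conclusion.** The point holds as an internal inconsistency in the order of allocation and baseline, with a plausible but unproven consequence for the primary outcome. Contamination of baseline AMMSA is a risk that the operational text leaves open. It requires that couples learn or infer their arm before they finish the questionnaires, which the article neither states nor rules out.

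The size and direction of any effect cannot be estimated, and no percentage loss of the planned effect should be attached to it. If the leak came through the avatar, it would concern exchange versus no exchange, hence mainly condition 1 versus condition 3. The matter should still be settled before the first couple is enrolled, because it concerns the reference value of the primary contrast and cannot be repaired later. The Results section states that recruitment had not begun as of January 2026.

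**What to change.** Make the rule in the Sample section the operating rule, in this order:

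1. Both partners complete and lock all baseline questionnaires.
2. The allocation is then released to session staff and to the couple, and not before.
3. Condition-specific avatar personification starts only after release. Avatar building that is the same in all arms may still overlap with the questionnaires.

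Reorder the description of phase 1 in Intervention Procedure accordingly. In Table 1, move the Baseline row and its tick ahead of "Allocation randomization". State explicitly when staff and couples each learn the arm.

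The cost is a somewhat longer session, by whatever part of avatar preparation can no longer run alongside the questionnaires, plus one table correction and a short text edit. Sample size, outcomes and the analysis model are unaffected.
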